## Abstract

**Background:** Tinnitus is a common problem worldwide. There is still no effective method to cure it. Traditional Chinese medicine (TCM) may be a potentially effective treatment approach for tinnitus. However, there is still no clinical trial with scientifically rigorous methodology to evaluate the treatment effect of TCM for tinnitus. Therefore, we propose a pilot study to inform the feasibility of a future full-scale RCT to establish the efficacy of TCM formula for tinnitus.

**Objectives:** The aim of this study is to determine the feasibility of a full-scale RCT and explore whether a TCM formula (BHT) has an additional effect on improving tinnitus when compared to informative counseling alone.

**Design:** An assessor-blinded, randomized, controlled clinical trial is used.

**Participants:** Twenty-four patients with chronic subjective tinnitus will be enrolled.

**Interventions:** The patients will be allocated randomly to receive a TCM formula (BHT, Bushen Huoxue Tongluo) and informative counseling or informative counseling alone. The oral BHT herbal granules will be taken twice per day continuously for 8 weeks.

**Main outcome measures:** The primary outcomes include recruitment rate, intervention completion rate, and data completion rate to evaluate the feasibility. The secondary outcomes include Tinnitus Handicap Inventory, tinnitus functional index, tinnitus sensation level, self-rated visual analogue scale on tinnitus loudness and annoyance, Pittsburgh Sleep Quality Index, Hospital Anxiety and Depression Scale, and adverse event. The outcome measures will be collected at baseline, end of treatment, and 4-week follow-up.

**Discussion**: This trial is currently ongoing and is recruiting patients. The expected study results will find some preliminary evidence about the clinical effectiveness of BHT on chronic tinnitus and will also determine if it is feasible to conduct a full-scale RCT of BHT and identify the necessary changes to the protocol if possible.

**Clinical Trial Registration:**
https://clinicaltrials.gov/, identifier ChiCTR2100046632.

## Introduction

Tinnitus is the perception of sound in the absence of external auditory stimulation. It is often described as a ringing, buzzing, or hissing sound in the ears or head. Tinnitus can be broadly classified into a subjective and an objective one. Objective tinnitus can be heard by others, and have its origin in vascular, muscular, skeletal, or respiratory structures (Henry et al., 2014). The vast majorities of those affected with tinnitus have a chronic subjective one, which is perceived only by the patient and not associated with an identifiable sound source (Henry et al., 2005; Tunkel et al., 2014). It is a common problem worldwide with a high prevalence. A systematic review reported in 2016 that the prevalence of tinnitus ranged from 5.1% to 42.7% globally with varied definitions (McCormack et al., 2016). It was estimated that about one in 10 adults has tinnitus in China and United States (Xu et al., 2011; Bhatt et al., 2016). The prevalence increases steadily with age, and it is more common in people aged between 40 and 70 years old (Henry et al., 2005). Chronic persistent, troublesome tinnitus can cause functional impairment in thought processing, concentration, sleep and even hearing, and also emotional disturbance, particularly anxiety and depression, all of which may substantially impact quality of life (Henry et al., 2005; Tunkel et al., 2014; Trevis et al., 2017). A survey in the United States has found that about half of the patients had discussed their problem with a physician (Bhatt et al., 2016).

The pathophysiology of tinnitus has not yet been completely understood. Tinnitus was traditionally thought to be a symptom resulting from inner ear damage; now, it is increasingly clear that tinnitus emerges from an intersection of both peripheral and central neurological pathways, contributors to which may involve medical (temporomandibular disorders and encephalitis), endocrinological, medication-related, or psychological factors (e.g., vulnerability–stress interactions) (Henry et al., 2014; Cheng et al., 2021). As no underlying cause is identified, the treatment of tinnitus is much challenging. There is still no scientifically validated medication or cure for this troublesome problem affecting millions of people (Tunkel et al., 2014). It has been reported that almost 60 different treatment modalities for tinnitus have been tried, including cognitive behavioral therapy (CBT), sound therapy, hearing aids, cochlear implants, pharmacotherapy, and acupuncture (Zenner et al., 2017). Sound therapies, such as tinnitus masking therapy, have been found to help relieve tinnitus. However, some patients may complain that they only substitute one unpleasant sound with a different one and interference with hearing (Henry et al., 2005). Antidepressants (such as the selective serotonin reuptake inhibitors), intratympanic steroids, or transcutaneous electrical nerve stimulation (TENS) have demonstrated improvement in severity of tinnitus; however, there is still insufficient robust evidence to support their application (Tunkel et al., 2014; Byun et al., 2020; Tutar et al., 2020). Now, only counseling and CBT are recommended to help patients mitigate the impact of tinnitus (Tunkel et al., 2014; Kallogjeri et al., 2017; Zenner et al., 2017).

There is still no United States Food and Drug Administration- or European Medicines Agency-approved drug on the market to treat tinnitus (Beebe et al., 2015).

Many people suffering from tinnitus seek help from complementary and alternative medicine (Enrico et al., 2007). Traditional Chinese medicine (TCM) is widely used to treat tinnitus in mainland China, Hong Kong, and other regions of East Asia. Many clinical studies on TCM treatment for tinnitus have been reported in recent decades. In Taiwan, a clinical trial on 21 patients has reported that a TCM formula Chai-Hu-Jia-Long-Gu-Mu-Li-Tang combined with Western medicine might have an additional effect on improving psychological sensation of tinnitus and sleep quality than Western medicine alone (Lin et al., 2015). In Japan, Yoku-kan-san, a TCM herbal formula, was found to cure tinnitus in 2 weeks on a patient enduring such a problem for 3 years (Okamoto et al., 2005). A systematic review in 2011 reported that the pooled analysis of 11 randomized controlled trials (RCTs) involving 1,231 patients with tinnitus suggested that TCM treatment might be more effective than Western medicines on improving the perception of tinnitus and some associated symptoms, such as headache, insomnia, dizzy, and vertigo (Wang and Zheng, 2011). Another systematic review in 2013 reported that TCM treatment combined with Western medicine showed a higher clinical effectiveness rate than Western medicine alone based on a pooled analysis of 18 RCTs (Wu and Hong, 2013). All these reviewed studies were conducted in mainland China with different TCM herbal formulae. The most popular herbs used in these formulae are Acori Tatarinowii Rhizome (Shichangpu), Puerariae Lobatae Radix (Gegen), Salviae Miltiorrhizae Radix et Rhizoma (Danshen), Astragali Radix (Huangqi), and Magnetitum (Cishi) (Wang and Zheng, 2011). Mechanism studies have indicated that TCM formulae could inhibit 5-HT (5-hydroxytryptamine)-induced RhoA/Rho kinase (ROCK) pathway, reduce pathologic damage of primary auditory cortex, or improve blood flow of meningeal microcirculation, which may contribute to the treatment of tinnitus (Zheng, 2006; Zhou et al., 2015; Wang et al., 2017). However, due to the poor reporting and some methodological flaws of these studies, no definite conclusion could be drawn on the TCM treatment effect on tinnitus.

Given the huge unmet clinical needs in the treatment of tinnitus and promising research findings of TCM treatment, it is worthwhile to further explore the TCM treatment for tinnitus. There is still no clinical trial with scientifically rigorous methodology to establish the treatment effect of TCM for tinnitus. There were three main problems in the previous studies. Firstly, there are some methodological limitations including no clear description of randomization and allocation concealment, no proper blinding, and no estimation of sample size (Wang and Zheng, 2011; Wu and Hong, 2013; Liu et al., 2016). Secondly, the TCM formula was applied without clearly defining the appropriate subset of patient population with corresponding syndrome or symptoms. According to TCM theory, a formula is generally organized to treat some syndrome under the guideline of treatment principle, which is developed based on TCM syndrome differentiation and thus aiming to manage some specific syndrome. Thirdly, validated and comprehensive outcome measures were seldom used. In mainland China, many self-developed scales or national evaluation criteria were used, which focused on evaluation of subjective feelings of patients about tinnitus and other associated symptoms (Wang and Zheng, 2011; Wu and Hong, 2013; Zhai et al., 2013). Such scales are not validated and difficult to be understood by Western medicine doctors.

We aim to evaluate the clinical efficacy and safety of TCM formula on chronic subjective tinnitus, in the hope of pursuing an effective treatment option for tinnitus. We have developed a TCM formula (BHT) for tinnitus based on previous studies and our clinical experience. An adequately powered RCT that compares TCM formula with placebo is appropriate to address the issue of efficacy; however, there is insufficient evidence to support a large full-scale RCT at present. Undertaking such a RCT raises important concerns including patients’ acceptance of TCM formula and adherence to treatment, as well as impact of TCM on the different aspects of tinnitus; furthermore, there is no previous study to provide some required parameters to design a definitive RCT. Therefore, we propose a small-scale pilot RCT to address whether a RCT of TCM formula for tinnitus is feasible with regard to (1) patient recruitment; (2) patient acceptability, (3) adherence to protocol, and (4) potential effectiveness of TCM formula. This pilot study is well justified by three main strengths on the study design. Firstly, a TCM formula BHT is developed based on the treatment principle of dredging the meridian passage and tonifying the essence of kidney, and prescribed to the subset of patients with corresponding TCM syndrome. Secondly, we will use validated and comprehensive scales to assess the impact and perception of tinnitus. Thirdly, we develop this study with scientific rigor following the CONSORT guideline extension to pilot study (Eldridge et al., 2016).

The natural course of subjective tinnitus varied considerably across individuals. The participants enrolled into clinical trials may demonstrate a small but statistically significant improvement, despite receiving no intervention (Phillips et al., 2018). A pilot randomized trial with controlled arm is more appropriate than an observatory study to provide preliminary data for further research. The results of this pilot study will inform a future full-scale RCT to establish the efficacy of TCM formula for chronic subjective tinnitus.

The study objectives are to determine the feasibility of performing a full-scale RCT for evaluating the effectiveness and safety of BHT for patients with chronic subjective tinnitus; to explore whether a TCM formula (BHT) has an additional effect on improving the impact of tinnitus in daily life and psychological function and also the perception of tinnitus after 8-week treatment and 4-week follow-up when compared to informative counseling alone; and to assess the safety of a TCM formula (BHT) in the patient population over the study duration of 12 weeks.

## Methods

### Design Overview

This pilot study is a randomized, assessor blind, two-arm, parallel superior trial. The trial design was developed conforming to Standard Protocol Items: Recommendations for Interventional Trials (SPIRIT) Guidelines (Chan et al., 2013). The study will be conducted in the Integrative Medical Centre (IMC), CUHK, and the Chinese Medicine Specialty Clinic cum Clinical Teaching and Research Centre at School of Chinese Medicine, CUHK. A total of 24 patients will be recruited and allocated randomly to receive a TCM formula (BHT) and informative counseling or informative counseling alone. The oral BHT herbal granules will be taken twice per day continuously for 8 weeks. The measures of feasibility and potential clinical effectiveness will be collected at baseline, end of the treatment (week 8), and after the follow-up (week 12). This trial will be conducted in accordance with the Declaration of Helsinki and ICH Good Clinical Practice.

### Subjects

#### Subjects Recruitment

The patients with chronic subjective tinnitus having no identified medical etiology will be recruited from the Otorhinolaryngology (ENT) Clinic in the Prince of Wales Hospital (PWH) and the Department of Otorhinolaryngology in the CUHK Medical Centre (CUHKMC), Hong Kong. Two Chinese medicine practitioners and two practicing otolaryngologists will work together to enroll eligible patients.

#### Specific Inclusion and Exclusion Criteria of Study Subjects

##### Inclusion Criteria

1) Diagnosis of unilateral or bilateral subjective continuous (24 h) tinnitus with normal hearing or bilateral/unilateral mild to moderate hearing loss, i.e., an average pure-tone audiometry threshold for 500, 1,000 and 2,000 Hz between 0 dB HL and 55 dB HL;2) Aged between 18 and 60 years old;3) Tinnitus duration of at least 6 months;4) Moderate level of distress caused by tinnitus with scores above 38 on the Chinese (Cantonese) version of the Tinnitus Handicap Inventory (THI-CH) (Newman et al., 1996; Kam et al., 2009);5) Having the diagnosis of TCM syndrome of kidney essence deficiency and stagnation of Qi and blood flowing in the meridian, which may have symptoms or signs of low back pain or general fatigue, frequent urination, and dark or pale tongue.

##### Exclusion Criteria

1) Has predisposing disease with tinnitus symptoms amenable to medical or surgical intervention;2) Has diagnosis of pulsatile tinnitus, somatosounds, or objective tinnitus;3) Has emotional, psychological, or psychiatric condition precluding full participation of the study;4) Has ever received any clinical treatment for tinnitus within the previous 1 month;5) Documented pregnant, breastfeeding, or planning pregnancy;6) Has ever taken any Chinese herbal medicine treatment in the previous 1 month;7) Has known history of allergy to Chinese herbal medicines;8) Has ever taken any anti-coagulant or anti-platelet agents other than low-dose (≤81 mg per day) aspirin;9) Has uncontrolled diabetes, hypertension or cardiac, liver, renal, cerebrovascular disease, or malignant diseases.

Subjects who meet every inclusion criterion and have none of the exclusion criteria will be eligible for inclusion in the study. Study candidates must be willing and able to provide written informed consent before entry into the study.

### Treatment Procedure

The eligible patients will be randomly allocated to receive TCM formula (BHT) granules and informative counseling or informative counseling alone. Two registered Chinese medicine practitioners (CMPs) with more than 5 years of clinical experience will be responsible for prescribing BHT to the patients. At the same time, the case history, signs and symptoms, and evaluation of tongue and pulse will be recorded with TCM diagnosis of syndrome.

#### Rationale and Composition of Chinese Herbal Formula BHT

According to Chinese medicine theory, the pathogenesis of chronic subjective tinnitus is mainly the insufficiency of essence to maintain the normal function of kidney and stagnation of Qi and blood flowing in the meridian through ear. So, the general treatment principle for tinnitus is to tonify the essence of kidney and dredge the meridian passage.

Following the treatment principle, we propose a Chinese herbal formula (Bushen Huoxue Tongluo Granules; BHT), which is modified from a classic TCM formula Er Long Zuo Ci Pill (耳聾左慈丸, in Chinese). The herbal compositions are shown in Supplementary Table S1.

Although no individualized syndrome differentiation is used in this study, this formula is designed following the core treatment strategy suitable for those patients with syndrome of kidney essence deficiency and Qi and blood stagnation, who generally have symptoms of low back pain, general fatigue, or dark or pale tongue from a Chinese medicine perspective. The prescription of BHT formula on such patients is the same as the ordinary clinical practice of Chinese medicine practitioner.

#### Preparation and Administration of BHT Granules

Concentrated Chinese medicine granules (CCMG) are used in this study, which are made from medicinal herbs by using modernized extraction and concentration technologies to replicate the traditional method of preparing medicinal decoction. All the herbal granules are manufactured by PuraPharm International (H.K.) Ltd., which is the only state-licensed CCMG brand in Hong Kong. Each granule used in BHT has been on the Hong Kong market for many years with separate wrapping and controlled quality.

The granules are used to improve the quality control elements of this study and reinforced the compliance of the participants. The pharmacy of Chinese Medicine Specialty Clinic will be responsible for preparing BHT granules into a mixture packaged in small single-dose sachets with a weight of 14.6 g. Patients in the treatment group will receive individually packaged doses of BHT, with each dose to be dissolved in warm water and consumed orally twice daily for 8 weeks.

#### Quality Control of BHT

High-performance liquid chromatography (HPLC) fingerprinting will be used for the quality control. We will choose catalpol, loganin, morroniside, paeonol, Tanshinone IIA, saikosaponin A, and puerarin (purity >98%, National Institute for the Control of Pharmaceutical and Biological Products) as reference compounds for quality control of BHT. The lab of Brain Research Center in CUHK will conduct the test.

#### Informative Counseling for all Subjects

Counseling will be provided by experienced audiologists about management in tinnitus. Subjects will be relieved about the epidemiology and nature of tinnitus. An explanation of the hearing test and tinnitus evaluation results will be explained by audiologist. Counseling will be provided at the beginning of intervention, and 4 and 8 weeks after the treatment.

The use of any other pharmaceutical agents, Chinese herbal medicines, or any other treatment approaches will be prohibited during the study period. We will provide general instructions on diet and lifestyle as usual clinical CM practice at the time of consultation. The patients will be asked to return for a clinical assessment from the CMP every 4 weeks.

### Randomization and Blinding

A computer-generated random allocation sequence through the block randomization method will be used. A research staff, with no clinical involvement in the trial, will be responsible for keeping the random allocation list and preparing sealed, opaque sequentially numbered envelopes, each containing a random number denoting the allocated treatment. After obtaining written informed consent, another research staff will open the envelopes serially, and refer the eligible patient to receive TCM formula (BHT) and informative counseling or informative counseling alone.

The outcome assessor will be kept blind at the intervention assignment during the whole study period. It is not feasible to blind doctors and patients in this study.

### Data Processing and Analysis

#### Baseline Assessment

All subjects will undergo otologic evaluation (including case history taking and otoscopic examination) and audiologic evaluation (including pure tone audiometry and tympanometry). Pure-tone audiometry (PTA) and tympanometry will be conducted to ensure that all subjects meet the inclusion criteria. Pure-tone air conduction thresholds will be measured at 250, 500, 1,000, 2,000, 3,000, 4,000, 6,000, and 8,000 Hz, and bone-conduction thresholds will be measured at 500, 1,000, 2,000, and 4,000 Hz using the standard Hughson-Westlake clinical procedure in 5-dB steps (Hughson and Westlake, 1994). High-frequency audiometry will also be performed at 10 kHz, 12.5 kHz, 16 kHz, and 20 kHz. The characteristics of tinnitus will involve measurement of parameters of self-perceived loudness in dB SL, pitch matching, and minimum masking level. Tinnitus pitch and loudness matching will be performed according to Vernon and Meikle’s procedure (Vernon and Meikle, 2003). Stimuli will be presented to the contralateral ear in cases of lateralized tinnitus, or randomly to either ear for bilateral tinnitus.

The following variables will be collected at baseline: age, gender, BMI, educational level, employment status, duration of tinnitus, percentage of tinnitus awareness during the day, and other coexisting health problems.

#### Primary Outcome Measures

The primary objective of this pilot study is to determine feasibility of a full-scale RCT. Specific outcomes include (1) recruitment rate, calculated as the percentage of eligible participants among those approached to determine if current eligibility criteria are too open or restrictive; (2) intervention completion rate, calculated as the percentage of recruited participants who complete the 8-week treatment (i.e., take ≥80% of the medicine); and (3) data completion rate, calculated as the percentage of recruited participants who complete the 8-week and 4-week follow-up assessments. The trial may be feasible if the recruitment rate ≥30%, intervention completion rate ≥80%, and data completion rate ≥80%, and not feasible if the recruitment rate <15%, intervention completion rate <70%, and data completion rate <70%. When the parameters fall between the two, it might be feasible if appropriate changes are made (Eldridge et al., 2016).

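### The recruitment rate is defined as eligible ÷ approached, so the recruitment criterion does not respond to refusals and can be met when few eligible patients join

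*Protocol article*

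**What the plan says.** All references are to the protocol article.

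- **Primary Outcome Measures** defines the first rate as "recruitment rate, calculated as the percentage of eligible participants among those approached to determine if current eligibility criteria are too open or restrictive". The second is the "percentage of recruited participants who complete the 8-week treatment", where completing means taking at least 80% of the medicine. The third is the "percentage of recruited participants who complete the 8-week and 4-week follow-up assessments".
- The same section sets the decision rule. The favourable limits, all percentages, are given as: "The trial may be feasible if the recruitment rate ≥30%, intervention completion rate ≥80%, and data completion rate ≥80". For the unfavourable limits, also percentages, the wording is: "not feasible if the recruitment rate <15%, intervention completion rate <70%, and data completion rate <70". Results between the two sets of limits are described as possibly feasible with changes.
- **Exclusion Criteria** says what eligible means: "Subjects who meet every inclusion criterion and have none of the exclusion criteria will be eligible for inclusion in the study". The text then gives consent as a separate condition, in a sentence of its own: "Study candidates must be willing and able to provide written informed consent before entry into the study".
- **Randomization and Blinding** places written consent before the allocation envelope is opened.
- **Introduction** says the pilot asks whether a trial is "feasible with regard to (1) patient recruitment; (2) patient acceptability, (3) adherence to protocol", with potential effectiveness as a fourth item.

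**The concern.** The label and the definition do not match. A recruitment rate should say how many of the patients approached, or of those who qualify, end up in the trial. The stated numerator stops one step earlier, at meeting the entry criteria. The stated purpose of the rate, finding out whether those criteria are too loose or too tight, fits an eligibility rate and does not fit recruitment.

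Feasibility is the primary objective, and recruitment is the first feasibility question in the Introduction. Willingness to join is a real unknown here: allocation is open to patients, the control arm receives counseling alone, and other treatments are prohibited during the study. If many eligible patients decline, the full-scale trial will need far more approaches or sites, and the pilot's recruitment criterion would give no sign of it.

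**Working it through.** **Inputs from the article.** Recruitment rate = eligible ÷ approached; cut-offs 30% and 15% (Primary Outcome Measures). Target enrolment 24 (Sample Size Estimation). Eligibility does not include consent (Exclusion Criteria; Randomization and Blinding).

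**Assumed input.** The article gives no consent rate among eligible patients, so it is varied from 5% to 100%. The eligibility rates below are illustrative too.

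**No figure to reproduce.** The article cites the CONSORT extension for pilot trials after the decision rule but shows no derivation of 30% or 15%, so the cut-offs cannot be rebuilt from the text.

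**Formulas.** Let e = eligible ÷ approached and c = randomised ÷ eligible.

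- Rate as defined in the protocol: e, with no dependence on c.
- Rate that counts joining: randomised ÷ approached = e × c.
- Approaches needed to enrol 24: 24 ÷ (e × c).

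**Single example.** 100 approached, 40 eligible, 6 randomised:

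- protocol rate: 40 ÷ 100 = 40%, above the 30% cut-off;
- randomised ÷ approached: 6 ÷ 100 = 6%, below 15%;
- randomised ÷ eligible: 6 ÷ 40 = 15%;
- approaches needed for 24: 24 ÷ 0.06 = 400.

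**Range, with eligibility held at e = 30%.** The protocol rate reads 30% on every row and so meets its cut-off.

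| Consent c (assumed) | Randomised ÷ approached | Approaches for 24 |
|---|---|---|
| 5% | 1.5% | 1,600 |
| 10% | 3% | 800 |
| 25% | 7.5% | 320 |
| 50% | 15% | 160 |
| 80% | 24% | 100 |
| 100% | 30% | 80 |

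From top to bottom the recruitment effort differs by 1,600 ÷ 80 = 20-fold, with the same reading on the protocol's rate.

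**Can the other two rates correct this?** No. Both have recruited patients as denominator. If 6 of 40 eligible patients join and all 6 complete, both rates are 100%. The secondary outcomes are tinnitus, sleep and mood measures and adverse events, and none of them measures uptake.

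**What happens if the existing cut-offs are moved unchanged to e × c?** Reaching 30% requires c = 0.30 ÷ e, and reaching 15% requires c = 0.15 ÷ e.

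| Eligibility e | Consent needed for 30% | Consent needed for 15% |
|---|---|---|
| 30% | 100% | 50% |
| 40% | 75% | 37.5% |
| 60% | 50% | 25% |

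The same two numbers are a much stricter test on the new rate, so they cannot simply be carried over.

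**The case against.** **Participants may mean people who joined.** On that reading the numerator would already be enrolled patients. It does not fit the rest of the text. The stated purpose is to test the eligibility criteria, consent is listed apart from eligibility, and the same section uses a different term, recruited participants, for the other two denominators.

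**Refusal would still be visible in the data.** This stands in part. The rate needs counts of approached and eligible patients, and the number randomised is known, so anyone could derive the consent rate. Heavy refusal would also show as slow accrual towards 24. What is missing is a criterion that reacts to it.

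**Acceptability is partly covered.** This also stands. Taking at least 80% of the medicine says something about acceptance of the formula among those who joined. Only willingness to join is unmeasured.

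**The recruitment cut-off does not decide feasibility alone.** Correct. It is one of three conditions for a favourable reading, and even that reading is worded as a possibility. The unfavourable conditions are joined by a conjunction, so read literally a low recruitment rate with good completion falls in the middle category and is not ruled infeasible. The error therefore lies in the recruitment component; it need not reverse the overall conclusion.

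**A stronger reading that fails.** A reader might infer that the definition also errs the other way, failing a selective but well-accepted trial. It does not. Since c cannot exceed 1, e × c can never exceed e, so counting randomised patients can only lower the rate and cannot rescue a trial with low eligibility. A low yield per approach is also a genuine feasibility signal, and it is what the stated rate was meant to detect.

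**Conclusion.** The point holds in one direction. The protocol calls an eligibility rate a recruitment rate and applies its 30% and 15% cut-offs to it. The recruitment criterion can therefore be met despite high refusal, and neither of the other primary rates would reveal this. Because the definition and cut-offs are written out in the article, this is a badly fixed outcome and not a detail left to a fuller plan.

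The actual size of the distortion is unknown, because the article gives neither an eligibility rate nor a consent rate. Under the assumed consent range of 5% to 100%, a protocol rate of 30% is compatible with anything from 1.5% to 30% of approached patients being randomised. The conclusion rests on the literal meaning of eligible, which the article's own handling of consent supports.

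**What to change.** 1. Rename the present measure the eligibility rate (eligible ÷ approached) and keep it for the question of whether the entry criteria are too loose or too tight.
2. Define the recruitment rate as randomised ÷ approached.
3. Report the consent rate, randomised ÷ eligible, as the measure of willingness to join.
4. Base the recruitment part of the decision rule on a rate that counts randomised patients. Re-justify or restate the 30% and 15% cut-offs for that rate, and do so before the feasibility data are reviewed.

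**Cost.** No extra patients, visits or procedures: only counts of approached, eligible and randomised patients, of which the first two are already needed for the stated rate. The Abstract says the trial is recruiting, so this is an amendment to a primary outcome definition during recruitment and should be dated and documented as such. The reported rate will be lower wherever any eligible patient declines.

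### The intervention completion rate counts all recruited participants but defines completion by medicine intake, so with about half the patients on counseling alone it cannot reach its own 80% threshold

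*Protocol article*

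**What the plan says.** Under Primary Outcome Measures, the protocol article makes feasibility the primary objective and gives three rates. The second is the "intervention completion rate, calculated as the percentage of recruited participants who complete the 8-week treatment (i.e., take ≥80% of the medicine"). Two sets of limits follow, both in per cent. The favourable set is "The trial may be feasible if the recruitment rate ≥30%, intervention completion rate ≥80%, and data completion rate ≥80". The unfavourable set is "not feasible if the recruitment rate <15%, intervention completion rate <70%, and data completion rate <70". Results between the two sets mean that a full trial might be feasible with changes.

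The design has two arms. Under Design Overview: "A total of 24 patients will be recruited and allocated randomly to receive a TCM formula (BHT) and informative counseling or informative counseling alone". Treatment Procedure repeats that patients are "randomly allocated to receive TCM formula (BHT) granules and informative counseling or informative counseling alone". The section on preparing the granules confines the medicine to one arm: "Patients in the treatment group will receive individually packaged doses of BHT". The counseling section closes off other medicines for everyone: "The use of any other pharmaceutical agents, Chinese herbal medicines, or any other treatment approaches will be prohibited during the study period".

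The article does not limit the denominator of the completion rate to the BHT arm, and it does not say what completing the intervention means for a patient who receives counseling alone.

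**The concern.** The numerator and denominator do not fit together. Completion is a matter of taking medicine, while the denominator includes patients who are given none. Taken at its word, the definition counts every counseling-only patient as a non-completer. An analyst who sees the problem may instead count controls as completers if they remain in the study, and then good retention among controls can make up for poor intake in the BHT arm.

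The Introduction lists "patients’ acceptance of TCM formula and adherence to treatment" among the concerns that justify a pilot. This rate is the only one of the three primary outcomes that addresses adherence to the medicine, and it feeds a numerical rule on whether to go on to a full-scale trial. If the denominator is settled only after the adherence data are known, that choice can decide whether the criterion is passed.

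**Working it through.** **Inputs.** Total of 24 patients (Design Overview; Sample Size Estimation). 10 per arm before dropout and 20% dropout (Sample Size Estimation). Thresholds of 80% and 70% (Primary Outcome Measures). Medicine in the BHT arm only (Treatment Procedure; Preparation and Administration of BHT Granules). True BHT adherence of 60% or 65%, and control completion of 80%, 90% or 100%, are assumptions for illustration; the article gives neither.

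**The plan's own total.** 2 × 10 = 20, and 20 × 1.2 = 24, which matches. Dividing instead gives 20/(1 − 0.2) = 25, a difference of one patient that does not matter here. Equal arms imply 24/2 = 12 per arm.

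**Counts needed on 24 patients.** 0.80 × 24 = 19.2, so at least 20 completers reach the upper line. 0.70 × 24 = 16.8, so at least 17 are needed to avoid falling below the lower line.

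**Reading 1: the text as written.** Only BHT patients can complete.
- Maximum rate with equal arms: 12/24 = 50%.
- Expected rate at 90% BHT adherence: 12 × 0.9/24 = 45%.
- With an uneven split of 14 to 10: at most 14/24 = 58%.
- Reaching 80% would need at least 20 of the 24 patients in the BHT arm.

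**Reading 2: controls count as completers if they stay in the study.** Let X ~ Bin(12, p) be the BHT completers and Y ~ Bin(12, c) the control completers. The pooled criterion is met if X + Y ≥ 20.
- If all 12 controls complete, 8/12 in the BHT arm (67%, itself under the lower line) gives (8 + 12)/24 = 83% and passes. Likewise 5/12 (42%) gives (5 + 12)/24 = 71% and clears the lower line.
- Chance of a pooled rate of at least 80%, P(X + Y ≥ 20), beside the chance on the BHT arm alone, P(X ≥ 10):

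| True BHT adherence p | Pooled, c = 100% | Pooled, c = 90% | Pooled, c = 80% | BHT arm alone |
|---|---|---|---|---|
| 65% | 58% | 33% | 17% | 15% |
| 60% | 44% | 23% | 11% | 8% |

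**Reading 3: BHT arm only.** 0.80 × 12 = 9.6, so 10/12 (83%) or more passes; 9/12 (75%) lies between the lines; 8/12 (67%) or fewer is below 70%. The chance of at least 10/12 is 25%, 56% or 89% at a true adherence of 70%, 80% or 90%. The exact (Clopper–Pearson) 95% interval for 10/12 is 52% to 98%.

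**How the rates combine.** The favourable verdict requires all three rates to reach their upper lines, so a completion rate of at most 50% rules it out. The unfavourable limits are also joined by 'and', so a low completion rate alone does not satisfy them.

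**The case against.** The strongest reply is that the authors plainly meant the BHT arm: a criterion about taking medicine applies to those who are given it, and no trial team would report the 50% ceiling as a finding. As a guess at intent this is plausible, and the fix adopts it. It is not what the text says. The data completion rate in the same sentence uses the same term for its denominator, recruited participants, and there it naturally covers both arms. Where the article wants a BHT-only measure it says so, as it does for kidney function under Secondary Outcome Measures.

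Two stronger readings are tempting, and the article supports neither.
- A reader might infer that the completion rate on its own condemns the trial as not feasible. It does not, because the lower limits are joined by 'and'. With good recruitment and data completion, the result falls in the middle zone.
- A reader might infer that pooling always hides poor adherence to a large extent. The 58% and 44% hold only if every control completes. At 80% control completion, in line with the planned 20% dropout, the pooled chances of 17% and 11% are close to the BHT-only 15% and 8%.

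It is also fair to say that the thresholds are softly worded, that the feasibility outcomes are reported descriptively, and that the right rate stays computable from intake data on the BHT patients. This limits the harm. It does not make the stated definition workable. Nor is this a detail left to an analysis plan: the article itself fixes the numerator, denominator and thresholds of a primary outcome.

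**Conclusion.** The point holds as an error in the stated definition of a primary feasibility outcome. As written, the rate is capped at about 50%, so its 80% criterion cannot be met and the favourable verdict is out of reach whatever the adherence. The cap of 50% assumes equal arms, which the 10 per arm implies but the article does not state as a ratio; the conclusion survives any split with fewer than 20 of 24 patients on BHT.

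Under the alternative that counts retained controls as completers, the distortion depends on control completion. At the assumed adherence of 60% to 65%, it runs from 2 or 3 percentage points in the chance of passing (80% control completion) to 36 or 43 points (100%). These figures also assume independent patients and 12 per arm.

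**What to change.** Redefine the rate in Primary Outcome Measures as the number of participants randomised to BHT who take at least 80% of the scheduled medicine, divided by all participants randomised to BHT. Apply the existing 80% and 70% thresholds to that rate and report it with its 95% confidence interval, preferably exact at this sample size. Report any counseling attendance separately by arm, outside this rate. The abstract says that recruitment is under way, so the change should be recorded before adherence data are examined.

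The change is to wording only and needs no additional patients or data on medicine intake. The price is a denominator of about 12 instead of 24 and hence a wide interval: an observed 10/12 passes the 80% line with an exact 95% interval of 52% to 98%, so the data would remain compatible with adherence well under 70%. The report should say so.
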